### Study settings

3.3

Nursing homes in the German‐speaking part of Switzerland, with and without a dementia unit, will be invited to participate in the study. Participating nursing homes will be randomly assigned to one of three sequences using a random number generator from the base 3.6.2 R‐package (R Core Team, 2020).

### Participants

3.4

Frontline nursing home staff and family members of PWD will be involved in this study. All inclusion criteria are detailed in Table 1. Potential nursing homes were identified by data‐mining lists from cantonal websites that contained accredited nursing homes and by referrals by cantonal Alzheimer associations.

**TABLE 1 jan14953-tbl-0001:** Inclusion criteria

Participant category	Inclusion criteria
People with dementia living in the nursing home	Not hospitalized during the recruitment phase and therefore physically present in the nursing home at the commencement of the study AND Diagnosis of vascular dementia or Alzheimer's disease OR People with symptoms indicating dementia which is documented in the nursing home records (BESA and RAI‐NH)
Family member of person with dementia	A family member/legal guardian of people with dementia as described above
Nursing home frontline staff	At least 18 years of age Employed at least 3 months in the respective organisation Must work at least 1 day per working week Able to communicate in German and follow the procedures of the study Provide continuing care to people with dementia
Nursing home	Provide continuing care to at least eight people with dementia

After obtaining consent from the nursing home management board, the participating nursing homes will assign a local clinical champion (Antunes et al., 2014; Bausewein et al., 2018). The clinical champion will screen subjects for eligibility using the criteria listed below and invite frontline staff, family members, attorneys (legal representatives) and PWD to separate introductory presentations and facilitate consent procedures.

### Intervention: IPOS‐Dem case studies

3.5

This description follows the template for intervention description and replication (TIDieR) (Hoffmann et al., 2014). Tailoring, modifications and adherence will be reported according to the last three TIDieR items in conjunction with the main results.

During the intervention, IPOS‐Dem observations from frontline staff and family members will be discussed during case studies. Each case study will include a 15‐ to 30‐min group discussion about the symptoms and concerns rated with the IPOS‐Dem instrument. Systematic case studies in nursing homes led by an intervention nurse will be encouraged (Boyd et al., 2014; Koppitz et al., 2016; Neylon, 2015). The intervention aims to reinforce the IPOS‐Dem care process changes identified by Ellis‐Smith (2018): (a) facilitated communication and collaboration among staff and family, (b) facilitated internal communication, (c) facilitated communication with external healthcare professionals and (d) care planning and changes to care provision. Case studies will follow the completed IPOS‐Dem instrument structure. The IPOS‐Dem instrument structure enables a systematic approach to discuss and reflect on the concrete issues of caring for PWD, despite the nursing homes’ differing local conditions. The local clinical champion will implement onsite activities (i.e., extending invitations to family members, preparing case studies and recording changes to care plans). An intervention nurse will lead moderation and deliberation during the case studies. The intervention nurse will be an advanced practice nurse with a PhD and expertise in chronic, palliative and dementia care. Frontline staff, the local clinical champion and family members will receive training (described later) to be sufficiently prepared for the case studies. On‐duty frontline staff and available family members will be present during these group case studies at the respective nursing home. The intervention nurse will lead the case studies monthly across rotating shift patterns for 12, 9 or 6 months, depending on randomization. The presence of staff and family members, the environment, and notes and resources (e.g., separate room and flip‐chart) will be adjusted according to the local conditions and regulations in the participating nursing homes. Family members are invited to attend in groups if they wish to. But they attend only the case study for their relative living in the nursing home. The intervention fidelity and adherence will be assessed using memos recorded by the intervention nurse.

### Training

3.6

Frontline staff and family members who have provided informed consent to participate in this study will be required to attend a mandatory introductory event 1–4 weeks before the baseline assessment. Separate 2‐h introductions will be held for frontline staff and family members. They will receive training in the study intervention and be introduced to the instruments for measuring outcomes: the IPOS‐Dem and QUALIDEM. The introductions will be conducted by members of the study team experienced in teaching and supporting staff (Pinto et al., 2018; Russell et al., 2016). A video recording of the introduction will be made available to those who cannot attend the introduction event in person. Follow‐up events will be scheduled every 3 months for frontline staff and family members to ask questions and clarify uncertainties about completing the instruments.

### Outcomes

3.7

We will assess the study outcomes in the sequence relative to the nursing home, as illustrated in Table 2. The scales and measures to be implemented are the German versions of the QUALIDEM (Dichter et al., 2011; Ettema et al., 2007a, 2007b) and the Swiss‐German adaptation of the IPOS‐Dem. Both the QUALIDEM and IPOS‐Dem will be assessed on a cluster and an individual nursing home level.

**TABLE 2 jan14953-tbl-0002:** Sequence of outcome assessment

Outcomes	Measured at the beginning of period
Socio‐demographics	T0
BESA/RAI MDS	T0
QUALIDEM	T0, T3, T6, T9, T12 and T14
IPOS‐Dem	T0, T1, T2, T3, T4, T5, T6, T7, T8, T9, T10, T11, T12, T13 and T14

#### Primary outcome: Caring quality measured with the QUALIDEM

3.7.1

The 18‐item QUALIDEM will be completed by nurses for each PWD in a 3‐month cycle, as shown in Table 2.

The QUALIDEM was developed to rate the quality of life, including caring quality for PWD living in residential settings by professional caregivers (Ettema et al., 2007b). For people with severe dementia, a short version with 18 items and a six‐subscale profile was validated (Dichter et al., 2016). The QUALIDEM subscales demonstrated Cronbach's alpha to be between 0.83 and 0.61 for the short version (Dichter et al., 2011) we will use. Ettema et al., (2007a) reported the original Dutch QUALIDEM inter‐rater reliability as modest, ranging from an intra‐class correlation (ICC) of 0.55 to 0.83 for the short version.

The individual subscale scores will be re‐calculated into a percentage score, as is usual for studies using the QUALIDEM (van Dam et al., ,^2019^, ^2020^; Dichter et al., 2015; Gräske et al., 2014; Oudman & Veurink, 2014). We will obtain an overall score by calculating the mean of the summed percentage scores.

We will calculate and illustrate longitudinal, total and individual subscale percentages for PWD to indicate the caring quality and quality of life trajectory.

#### Secondary outcome: Symptoms and concerns measured with the IPOS‐Dem

3.7.2

We will report on the secondary outcome (symptoms and concerns) by calculating the total score composed of the 27 given IPOS‐Dem items assessed for the PWD by frontline staff and family members. IPOS‐Dem data will be collected at the beginning of every period, that is, monthly, as shown in Table 2, by frontline staff and family members.

The IPOS‐Dem is a questionnaire designed to be completed by carers. It contains 27 items about common and additional needs and concerns of PWD. Each item is scored on a five‐point scale ranging from 0 (no concern) to 4 (overwhelming) (Cicely Saunders Institute (CSI), 2018b).

The IPOS‐Dem was developed for the nursing home setting, where its introduction to routine care was established as feasible and acceptable (Ellis‐Smith et al., 2017, 2018). The reliability and validity of the Swiss‐German adaptation of the IPOS‐Dem will be assessed during the first 3 months of this project. We intend to detail the psychometric validation elsewhere.

Furthermore, subgroup comparisons between single‐item and subscale percentages or respective scores between the QUALIDEM and IPOS‐Dem will be tested.

### Recruitment, consent and data collection

3.8

The project leaders will arrange meetings with the nursing home management boards to introduce the study. The suitability and availability of the nursing home for inclusion in the study will be discussed. If a nursing home management board agrees to participate in the study, a trial agreement will be signed by the head of the nursing home and the University of Applied Sciences and Arts Western Switzerland (HES‐SO), School of Health Fribourg.

We will provide all study participants, as outlined in Table 1, with appropriate information sheets and respective consent forms that describe the study and with sufficient information for the participants (and, if applicable, their attorneys) to make an informed decision about their participation. We will give the participants (and, if applicable, their attorneys) as much time as they need to make an informed decision.

The rationale for this study, which is to critically improve caring quality and quality of life for PWD in nursing homes in the future, will be emphasized to participants and communicated so that everyone can understand (Hanson et al., 2014). A research staff team member will also be present in the nursing homes regularly to offer flexibility in how PWD are informed about and consent to inclusion in the study (Hanson et al., 2014). Participants and study sites will be able to withdraw from the study procedures at any time. The informed consent will include information to confirm that the submitted anonymized data will be used until the decision to withdraw consent.

For eligible participants, the following baseline data will be captured:
Demographics of PWD (age, gender, marital status, care dependency (Schmid, 2019), dementia type and severity).Demographics of family members (age, gender, marital status and relation to the person with dementia).Demographics of frontline staff (age, gender, professional role, highest completed education, type of palliative care training and the number of years of working experience).The latest documentation within RAI or BESA.

The clinical champion assigned in each nursing home (Antunes et al., 2014; Bausewein et al., 2018) will primarily oversee the measurements of the IPOS‐Dem and QUALIDEM. The IPOS‐Dem measurement will take place monthly (T0–T14). A study team member will be responsible for ensuring that all the scheduled measurements are conducted by reminding and supporting the clinical champions and the clinical contact person at each site. The clinical champion will ensure that the QUALIDEM is measured and completed at the time points specified in Table 2.

### Sample size calculation

3.9

The sample size was calculated using simulations for a cohort stepped‐wedge design. The primary outcome would be repeatedly obtained from the same participants within each cluster (nursing home), as in previous similar studies (Aegerter et al., 2020). Based on previous QUALIDEM results, we assumed a baseline mean of 71.3 and a standard deviation of 16.7 (van Dam et al., 2019). The number of nursing homes was set to 20 with three cluster groups. The attributable difference in the QUALIDEM was expected to be around 5%, as derived from clinical expertise. We set the number of steps to three for practical reasons (study rollout). After baseline measurement, nursing homes will switch from the control condition to the intervention condition at given periods until all nursing homes are applying the intervention regime. To determine the appropriate sample size, we varied the average cluster size in our simulation over a range of 4 to 16 subjects per cluster. We assessed the sensitivity of the sample size calculations by varying the cluster‐specific and subject‐specific ICC. More specifically, we used ICC values for Rho[1] = {0.1, 0.2} and Rho[2] = {0.2, 0.3}, respectively. In our simulation, we used a standard closed cohort mixed‐effects model. The latter comprised a random effect for the clusters (*α*) and a random effect for the repeated measurements on the same cohort of individuals (*ζ*). Moreover, the model included a fixed effect to account for time trends (*β*) and a fixed effect representing the treatment effect (*θ*).
(1)
$$y=\mu_{\mathrm{ij}}+e_{\mathrm{ijk}}$$

(2)
$$\mu_{\mathrm{ij}}=\mu +\alpha_{i}+\zeta_{\mathrm{ik}}+\beta_{j}+X_{\mathrm{ij}}\theta$$

(3)
$$\zeta_{\mathrm{ik}}∼N\left(0,\sigma_{\zeta }^{2}\right)$$

(4)
$$\alpha_{i}∼N\left(0,\sigma_{\alpha }^{2}\right)$$

(5)
$$e_{\mathrm{ijk}}∼N\left(0,\sigma_{e}^{2}\right)$$

To estimate our models, we used the linear mixed‐effect method (lmer) from the R‐package lme4 (Bolker et al., 2021). Furthermore, we set the acceptance probability for a Type I Error to *p* = .05 and the acceptance probability for a Type II Error to *p* = .20 (power = 0.80).

The required sample sizes to achieve the desired power of 0.80, given the aforementioned parameters and assumptions, are shown in the two scenarios plotted in Figure 1.

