**FIGURE 1 jan14953-fig-0001:**
[figure not shown]
Power and sample size over a varying range of the mean number of subjects per cluster

Overall, a higher ICC yielded a lower total number of subjects needed to achieve the desired power (Figure 1, panel b compared with a). We found the solution with 200 participants, 20 nursing homes and three steps (Figure 1a) to be optimal because three steps put much less burden on participants and study staff than a greater number of steps. On the other hand, the proposed ICCs are more conservative. Furthermore, it seems highly feasible to administer the intervention to participants in the randomized clusters within three steps. To account for attrition, we further adjusted the required sample size. Husebø et al., (2019) and Chenoweth et al., (2011) reported 20–25% attrition. We increased the number of clusters from 20 to 22 to address the risk of underpowering our study. To summarize, our study will enrol and follow 220 participants in 22 clusters over six discrete measurements (one at baseline and five during the control and intervention conditions), which will yield a total of 1320 observations. We do not intend to conduct interim analyses of the outcomes.

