### Statistical analyses

3.11

The data will be analysed on an ‘intention to treat’ basis and analysed per protocol to verify the intention to treat results, as in previous similar studies (Aegerter et al., 2020). Missing data will be examined using the R‐package naniar 0.5 (Tierney, 2021) and multiple imputations will be used if required.

Linear mixed‐effects will be used to assess intervention effects on our primary outcome measured using the QUALIDEM over the study period. The broader category of generalized linear mixed‐effects models (GLMMs) will also be used to analyse secondary outcomes. GLMMs are extremely flexible since they support various distributions of the outcome variable, such as Gaussian, Bernoulli, binomial, gamma, negative binomial, ordinal and Poisson, as well as several link functions (e.g., identity, log, logit, probit and log‐log) (Cnaan et al., 1997; Lindstrom & Bates, 1990). Moreover, these models will handle non‐normal data and adjust the effects of clustering. Individuals will be nested in each cluster, and individuals will be measured at baseline and at five additional time points (Hemming et al., 2018; Luke, 2019).

Consequently, we will use GLMMs to investigate secondary outcomes, such as the symptoms and concerns of PWD. All models will be adjusted for potential confounding factors, such as age, gender, marital status, care dependence, dementia type and severity at baseline. All statistical analyses will be performed using R statistical software (R Core Team, 2020).

An alpha level of 0.05 will be accepted as significant. The results of the mixed‐effects modelling will be presented in outcome‐specific effect sizes, including the corresponding 95% confidence intervals.

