Therefore, we propose to evaluate a novel case studies intervention based on accessible systematic observation of needs and concerns by family members and frontline staff. The case studies intervention is conducted by an expert nurse external to the nursing home, trained to encourage open discussion and bottom–up management needs and concerns in PWD participating in the study. We expect to encounter heterogeneity in Swiss nursing homes regarding the needs and concerns of PWD and organization, leadership, staffing and grade mix. Therefore, to account for the complexity of the intervention, we planned the study with an SW‐CRT design. SW‐CRTs have been shown to work well in the exploratory phase of developing complex interventions (Craig et al., 2008).

On the one hand, our decision to conduct an SW‐CRT reconciles the practical ethical and logistical concerns another trial may have posed for the PWD, us and the nursing home managers involved and the research team. On the other hand, there are drawbacks to employing this design: an SW‐CRT usually requires a larger sample size than the corresponding designs; also with the staggered starting times, the study duration is increased (Haines & Hemming, 2018; Hemming, Haines, et al., 2015). However, since blinding frontline staff and family members (i.e., the outcome assessors) is not possible in our study, we proceed with utmost care to reduce the risk of bias (Hemming et al., 2018; Siebenhofer et al., 2018). The increased sample size and, therefore, nursing homes contribute data on both intervention and control condition. The resulting datasets will be made accessible to interpret and apply to international long‐term care contexts.

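### The power simulation has no home-by-period random effect: it fixes the cluster autocorrelation at 1, never varies it, and overstates power if homes drift differently over time

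*Protocol article*

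**What the plan says.** Section 3.9 writes the model out in equations (1) to (5): a grand mean, a random home effect, a random resident effect, a fixed effect for each period shared by all homes, the treatment effect and residual error. The resident term is described as "a random effect for the repeated measurements on the same cohort of individuals". The inputs are stated: "we assumed a baseline mean of 71.3 and a standard deviation of 16.7", "The attributable difference in the QUALIDEM was expected to be around 5" per cent, and "The number of nursing homes was set to 20 with three cluster groups". Sensitivity is examined by varying two quantities only, the cluster ICC (0.1 or 0.2) and the subject ICC (0.2 or 0.3).

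The text with Figure 1 reports that "a higher ICC yielded a lower total number of subjects needed to achieve the desired power". It settles on 200 residents in 20 homes under the lower ICCs and calls those ICCs the more conservative choice. Two homes are then added for attrition, which cited studies put at 20–25%.

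Section 3.2 (Design) and section 3.11 (Statistical analyses) describe the analysis in words. Both name the same two levels, homes and individuals measured repeatedly. Neither writes out a random-effects formula.

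**The concern.** Under this model, two residents of one home are as strongly correlated in the same quarter as they are 14 months apart. In a stepped wedge the treatment effect is estimated largely from changes within homes over time. Home-specific change over time is the variance component that the model sets to zero, and zero is its most favourable value.

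The article gives reasons to think it may not be zero. Homes may start on different calendar dates (section 3.2), so a season, an outbreak or a staffing shock reaches different homes in different study periods, and a common period effect cannot absorb it. Section 3.2 also expects a learning curve among staff, which need not have the same shape everywhere. QUALIDEM is completed by nurses (section 3.7.1), and the Discussion says that outcome assessors cannot be blinded, so a change of raters or of rating habits can shift a whole home at once.

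Two things are at stake: the stated power, and the validity of the primary test if the same structure is carried into the analysis.

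**Working it through.** **Inputs from the article.** SD 16.7, so total variance 278.89; difference 5 points on the 0–100 score; 20 homes of 10 residents; three sequences; six QUALIDEM measurements (T0, T3, T6, T9, T12, T14); crossover at months 3, 6 and 9; alpha 0.05; target power 0.80.

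**Assumptions of this check.** Two-sided test; homes split 7/7/6; the measurement at the crossover month counted as exposed; complete data. The meaning of Rho[2] is not stated, so two readings are carried:

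- Reading A: 0.2 is the total within-resident correlation. Variance shares are home 0.1, resident 0.1, residual 0.8.
- Reading B: 0.2 is an additional share. Variance shares are home 0.1, resident 0.2, residual 0.7.

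**Method.** Let va, vg, vz and ve be the home, home-by-period, resident and residual variances, and m = 10. The six period means of one home have covariance (va + vz/m)J + (vg + ve/m)I, where J is the matrix of ones and I the identity. Generalised least squares with fixed period effects gives the SE of the treatment effect. Power = Φ(5/SE − 1.96). The article's model is vg = 0. For CAC = c, the home share is split into va = c × share and vg = (1 − c) × share, so total variance and within-period ICC stay fixed.

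**Reproducing the stated figure.** Reading A, CAC 1: va = vz = 27.89, ve = 223.11, SE = 1.808. Power = Φ(2.765 − 1.96) = Φ(0.805) = 0.790, against a stated 0.80. REML simulation (3,000 runs) gives 0.794. Reading B with six measurements gives SE 1.697 and power 0.838; with four periods it gives 0.787. Taking the 5% as relative (3.565 points) gives only about 0.50, so the absolute reading is used.

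**Adding drift.** Reading A, CAC 0.8: vg = 0.2 × 27.89 = 5.58. The part of a home-period mean's variance that is independent between periods rises from 22.31 to 22.31 + 5.58 = 27.89. SE becomes 2.006, and power = Φ(2.493 − 1.96) = Φ(0.533) = 0.703.

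| CAC | Lower ICCs, A | Lower ICCs, B | Higher ICCs, A | Higher ICCs, B |
|---|---|---|---|---|
| 1.0 | 0.790 | 0.838 | 0.834 | 0.933 |
| 0.9 | 0.744 | 0.790 | 0.737 | 0.834 |
| 0.8 | 0.703 | 0.744 | 0.653 | 0.737 |
| 0.6 | 0.632 | 0.665 | 0.530 | 0.585 |

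The higher ICCs are the pair 0.2 and 0.3. Under reading A, 80% power at the lower ICCs needs about 20.5 homes at CAC 1, 22.9 at 0.9, 25.3 at 0.8 and 29.7 at 0.6. With 22 homes and no attrition, reading A gives 0.833, 0.791 and 0.751 at CAC 1, 0.9 and 0.8.

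**The ICC ordering.** At CAC 1 the higher ICCs give more power under both readings, as the article says. Under reading A the order has reversed by CAC 0.9 (0.737 against 0.744). Under reading B the higher ICCs still lead at 0.9 (0.834 against 0.790), and the order reverses only near 0.8 (0.737 against 0.744).

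**Type I error if the simulation model is also the analysis model.** At the lower ICCs under reading A, the model reports an SE of 1.82 against a true 1.91 at CAC 0.9, and 1.83 against 2.01 at CAC 0.8. Type I error = 2Φ(−1.96 × reported/true), which is 6.2% and 7.5%; REML simulation gives 6.8% and 7.3%. Reading B with 22 homes, by simulation, gives 6.0% and 8.5%. At the higher ICCs with CAC 0.8 the figures are 10.7% (A) and 11.9% (B). At CAC 1 the same model gives 5.1–5.4%. With the home-by-period term included, simulated rates are 5–6%.

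**The case against.** The strongest reply is that equations (1) to (5) are introduced as the simulation model, while section 3.11 gives no random-effects formula. The SAP and the analysis code are not shown and may contain the extra term. That stands. A reader might infer that the planned primary analysis is known to give standard errors that are too small. The article does not establish this; it only names the same two levels in sections 3.2 and 3.11. The type I error figures are therefore conditional. The power figure and the remark on ICCs are not affected by this reply, because both stand in section 3.9.

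A second reply is that no CAC is given, so the size is unknown. That also stands. With no drift the loss is zero. At CAC 0.9 it is about 5 points, and reading B then still gives 0.790.

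A reader might also take the Discussion's "We expect to encounter heterogeneity in Swiss nursing homes regarding the needs and concerns of PWD and organization, leadership, staffing and grade mix" as evidence of drift. It is not: it describes differences between homes, and stable differences are what the home intercept absorbs. The case for drift rests on staggered start dates, the learning curve and unblinded raters, none of which the article quantifies.

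Finally, a reader might infer that the ICC ordering holds only at a CAC of exactly 1. That goes too far: under reading B the ordering survives at 0.9.

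**Conclusion.** The point holds in conditional form. The only model written out omits home-by-period variation, and the sensitivity analysis never varies it, so the 80% power is the value for no home-specific drift. For any positive home-by-period variance examined, true power is lower: by 9 points at CAC 0.8 under either reading, and by 16 to 17 points at CAC 0.6. The two extra homes are already committed to attrition and are no reserve for this. Calling the lower ICCs conservative is right only when CAC is close to 1. Inflation of the type I error follows only if the same structure is used for the primary analysis, which the article suggests but does not fix. All sizes rest on an assumed CAC, a 5-point absolute difference and complete data.

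**What to change.** 1. Specify the primary model with a random home-by-period effect, in lme4 terms (1|home) + (1|home:period) + (1|resident), and a small-sample correction suited to about 22 clusters (Kenward–Roger or Satterthwaite). If the SAP already does so, say so and make the simulation match.
2. Rerun the power simulation with this model over a stated, assumed CAC range, for example 0.6, 0.8, 0.9 and 1.0. Report the resulting range of power, and define Rho[2] so that the calculation can be reproduced.
3. Qualify the statement on ICCs: a higher ICC needs fewer subjects, and the lower pair is the cautious choice, only when CAC is close to 1.

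The cost is one more term in code that already uses lmer, one rerun of the simulation, a lower stated power and slightly wider intervals. If there is no drift, the added variance should be estimated near zero and little is lost.

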### Design

3.2

We propose a stepped‐wedge cluster randomized trial (SW‐CRT) design (Hemming et al., 2015; Hemming et al., 2015) to examine the objectives. An SW‐CRT starts without exposing the clusters, nursing homes in our case, to the intervention to allow for baseline data collection. During study conduct, the clusters or cluster groups are exposed to the intervention in a step‐wise fashion, occurring after regular intervals until all clusters are exposed to the intervention. We will employ mixed‐effects models, i.e., random effects, to adjust for cluster‐specific factors and repeated measures design. This trial will evaluate whether structured symptom assessment and subsequent case studies augment caring quality for PWD. The intervention will be assessed by (1) caring quality with the QUALIDEM and (2) changes in identified needs, as assessed by the IPOS‐Dem.

The SW‐CRT has three advantages for our study. Firstly, the design allows long‐term effects, i.e., trends, to be assessed during the study (Jordan et al., 2015). One expected trend is that the caring quality, as measured by the QUALIDEM, will improve over time. The implementation of purposive data collection using the IPOS‐Dem, representing the control condition, could also be interpreted as a trend by itself, with a learning curve for frontline staff. The stepped‐wedge design will enable an objective assessment of both trends during the trial. Secondly, we aim to offer nursing home management boards added value for their residents through using an SW‐CRT because exposure to the case study intervention for 6 months is guaranteed. Thirdly, our case study intervention is dependent on the observations of frontline staff and family members using IPOS‐Dem, which promotes inclusivity and participation. Introducing the intervention en bloc was considered challenging regarding logistics regarding the aforementioned prerequisite and the complexity of the case study intervention. Therefore, we will employ measurements at fixed periods across the trial duration in participating nursing homes and consider the time effects in the models for analysis (Haines & Hemming, 2018). In other words, the presumed effect of the implementation of the IPOS‐Dem and QUALIDEM will be levelled out by the time the intervention commences.

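### The only treatment term the protocol gives is one constant effect; if the effect of monthly case studies builds up beyond three months, that term understates it, so an exposure-time model should be pre-specified beside it

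*Protocol article*

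**What the plan says.** Section 3.9 of the protocol article writes out a closed-cohort mixed model with random effects for home and for resident. For calendar time, "the model included a fixed effect to account for time trends"; for the intervention there is "a fixed effect representing the treatment effect", entered in equation 2 as X_ij times theta. There is no lag, exposure-time or treatment-by-time term. Section 3.11 says that linear mixed-effects models will assess the intervention on QUALIDEM over the study period. It neither restates equation 2 nor gives another form for the effect.

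Section 3.5 describes the exposure: "The intervention nurse will lead the case studies monthly across rotating shift patterns for 12, 9 or 6 months, depending on randomization". Section 3.2 places the crossovers at 3, 6 and 9 months. Table 2 places QUALIDEM at T0, T3, T6, T9, T12 and T14, each at the beginning of a period.

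**The concern.** One theta means that the full effect is present at the first exposed QUALIDEM and stays the same. With the crossover-month visit counted as control, that first visit comes three months after crossover. Case studies repeated monthly, and aimed at communication and care planning, may plausibly take longer than that to show their full effect.

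In a stepped wedge, homes already exposed serve as comparators for homes exposed later. This happens at T9, and for all homes at T12 and T14. If the effect is still growing in the early homes, part of the growth is taken up by the common period effects and then subtracted from the later homes. Theta is then not an average of the effects reached, and an intervention that works slowly could be reported as ineffective.

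**Working it through.** **Inputs.** From section 3.9: "we assumed a baseline mean of 71.3 and a standard deviation of 16.7"; "The attributable difference in the QUALIDEM was expected to be around 5" per cent, read as 5 points on the percentage score; ICCs 0.1 (home) and 0.2 (resident). From section 3.11: "An alpha level of 0.05 will be accepted as significant", taken as two-sided. Schedule and crossovers are as above. My assumptions are an allocation of 7/7/6 for 20 homes and 7/7/8 for 22, no attrition, and the crossover-month visit counted as control.

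**Method.** Generalised least squares on home-by-visit means with six period effects and

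V = (σ_e²/n) I + (σ_α² + σ_ζ²/n) J, n = 10.

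Total variance is 16.7² = 278.89. With the resident ICC as an additional share, σ_α² = 27.89, σ_ζ² = 55.78 and σ_e² = 195.22. Power = Φ(effect/SE − 1.96).

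**The plan's own figure.** The target is stated as "The required sample sizes to achieve the desired power of 0.80", met by 200 residents in 20 homes. A constant effect of 5 gives SE 1.81 and power 0.79 if the resident ICC includes the home part, and SE 1.70 and power 0.84 if it is additional. The stated figure is reproduced, so the model is being read as intended.

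**Exposure at each visit.** Sequence 1: 3, 6, 9 and 11 months. Sequence 2: 3, 6 and 8. Sequence 3: 3 and 5. With 22 homes there are 28 + 21 + 16 = 65 home-visits under intervention: 22 at 3 months, 8 at 5, 14 at 6, and 7 each at 8, 9 and 11.

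**Weights in theta** (22 homes of 10, SE 1.60):

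| Exposure (months) | 3 | 5 | 6 | 8 | 9 | 11 |
|---|---|---|---|---|---|---|
| Weight | +0.964 | +0.153 | +0.182 | -0.006 | -0.146 | -0.146 |

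Grouped, these are +0.96 at 3 months, +0.33 at 5–6, -0.15 at 8–9 and -0.15 at 11. They sum to 1, so a constant effect is recovered exactly.

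**Worked case: linear rise to 5 points at 6 months.** The effects are 2.5 at 3 months, 4.17 at 5, and 5 from 6 on.

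- Expected theta = 0.964 × 2.5 + 0.153 × 4.17 + (0.182 − 0.006 − 0.146 − 0.146) × 5 = 2.41 + 0.64 − 0.58 ≈ 2.5.
- Mean over intervention measurements = (22 × 2.5 + 8 × 4.17 + 35 × 5)/65 = 263.3/65 = 4.05.

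**All cases:**

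| Assumed effect | Expected theta | Mean over intervention measurements | Ratio | Power |
|---|---|---|---|---|
| 5 points, complete by 3 months | 5.0 | 5.0 | 1.00 | 0.88 |
| rises to 5 by 4 months | 3.8 | 4.6 | 0.83 | 0.66 |
| rises to 5 by 6 months | 2.5 | 4.05 | 0.61 | 0.34 |
| rises to 5 by 9 months | 1.15 | 3.2 | 0.36 | 0.11 |
| rises to 5 by 11 months | 0.8 | 2.7 | 0.30 | 0.07 |
| 5 up to 6 months, then 2.5 | 5.75 | 4.2 | 1.37 | 0.95 |

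Reading the resident ICC as including the home part moves theta by at most about 0.03.

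**Alternative model.** With separate effects at 3, 5–6, 8–9 and 11 months, the average of the first two has SE 1.87. Its expected value is 4.4, 3.7, 2.5 and 2.05 for the four rising curves. The average of all four has SE 2.51.

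**The case against.** The strongest reply is that equation 2 belongs to the sample-size simulation, where a constant effect is an ordinary simplification. Section 3.11 does not adopt it in so many words, and a supporting model is the kind of detail often left to an analysis plan that is not shown here. This stands to the extent that the point is an improvement and not an error or contradiction. It does not remove the point, because equation 2 is the only form of the treatment effect in the document and the sample size rests on it.

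Three stronger readings are tempting and are not supported.

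- **That the protocol sets out to estimate a growing intervention effect.** Section 3.2 says that the design lets long-term effects be assessed, and adds: "One expected trend is that the caring quality, as measured by the QUALIDEM, will improve over time". That passage equates long-term effects with trends over time and describes a learning curve under the control condition. Its stated answer is time effects in the model. It does not promise an effect by length of exposure.
- **That theta is always far too low.** The documents give no effect curve and do not say that the effect is cumulative. There is no bias if the effect is complete by three months, and a 17% shortfall if by four. A fading effect is overstated.
- **That the gap is larger still.** Averaging the six exposure lengths equally gives 4.4, 3.7 and 3.2 for the 6-, 9- and 11-month curves, and 3.75 for fading. But exposures of 8, 9 and 11 months each occur in one sequence only, so the mean over actual measurements is the fairer comparison.

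In the other direction, counting the crossover-month visit as control is the milder assumption. The protocol does not state this coding. If the visit counted as intervention, even a three-month build-up would be estimated near zero.

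**Conclusion.** The point holds as a conditional one. The negative weights after about eight months follow from the schedule and the constant-effect term, whatever the true curve. Whether they matter depends on the curve: theta would recover between all and about 30% of the mean effect over intervention measurements, from completion by 3 months to a linear rise over 11, and would exceed that mean by about 37% in the fading case.

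This rests on equation 2 being the analysis model, the crossover-month visit counting as control, a 7/7/8 split, ICCs of 0.1/0.2 and no attrition. It does not show that the trial will miss its effect. It shows that a null theta alone could not separate no effect from a slow one. Pre-specifying a second model is a cheap safeguard that the plan should take up.

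**What to change.** Keep the constant-effect model as primary. Before outcome data are seen, add to section 3.11:

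- a supporting model with the same random and period effects, and separate intervention effects at 3, 5–6, 8–9 and 11 months since crossover, with the crossover-month visit counted as control;
- as its reported summary, the average of the 3-month and 5–6-month effects, which every sequence reaches;
- a rule that a null constant effect is not interpreted as no effect unless this supporting estimate agrees.

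This needs a few more fixed-effect terms and no new homes, visits or residents. The cost is precision: SE about 1.87 against 1.60, so a 95% half-width of about 3.7 points (1.96 × 1.87) against 3.1 (1.96 × 1.60), before attrition. The summary describes the effect over roughly the first six months. It does not stand in for the effect at 8 to 11 months, which only the earlier sequences reach. Averaging over all four categories would cover that, at an SE of 2.51.
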